### Treatment allocation and randomization

Dyads will be randomized (1:1) to the intervention (*MatchQEP*) or control (*Match*) group prior to baseline assessment. Treatment allocation will be centrally randomized using a web-based scheme (https://www.randomizer.org/). The randomization will be completed by a PhD student external to the research team and group allocation will be assigned in the order in which participants have completed an initial background and demographics questionnaire and have been matched with a peer for the study. Although the research coordinator(s), QEPs, and participants cannot be blinded to treatment allocation, the primary investigators and statistician completing data analysis will be blinded.

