**Fig. 1 Fig1:**
[figure not shown]
Actor-Partner Interdependence Model framework for indistinguishable dyads testing the effects of breast cancer survivor peers on moderate-to-vigorous physical activity (X = Baseline, Y = Post-10 week intervention as primary endpoint)

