### Data collection and measures

Following informed consent, all BCS will complete a demographics questionnaire, including questions related to peer matching criteria, treatment, and exercise history. To determine the effectiveness of the intervention, BCS will complete exercise volume, social support, and HRQOL questionnaires online at four time points: baseline, post 10-week intervention, post 4-week tapering (i.e., 14 weeks post-baseline), and at 12 weeks post-intervention follow-up (i.e., 26 weeks post-baseline). BCS will be asked to wear the Fitbit to collect device-measured MVPA for one week at all four timepoints. Self-reported sedentary behavior will be assessed as a potential covariate at all time points. The QEP alliance (i.e., connection to the QEP support provider) will be assessed as a covariate at post-intervention and post-tapering time points. Adherence to the intervention will be calculated at the end of the intervention period (10 weeks) and cost-effectiveness will be assessed at post-intervention (10 weeks), post-tapering (14 weeks), and at the 12-week post-intervention follow-up (26 weeks after baseline assessment).

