### Primary outcome

Exercise volume at the post 10-week intervention time point, will be measured using a valid and reliable self-report survey (modified Godin Leisure Time Exercise Questionnaire) [56–58]. The modified Godin Leisure Time Exercise Questionnaire is a self-report measure which asks respondents to give weekly frequencies and durations of strenuous, moderate, and mild aerobic activities. Resistance training volume will also be self-reported using the same format as the aerobic activities (e.g., frequency and time metrics). Responses on moderate and strenuous activities are summed to determine total MVPA volume. This measure will also be assessed at the post-tapering (i.e., 14-weeks) and 12 weeks post-intervention follow-up (i.e., 26 weeks post-baseline) time points.

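### Randomisation precedes the baseline assessment in an unblinded trial with no stated concealment until baseline is done, so the self-reported MVPA that adjusts the primary comparison is a post-randomisation measure

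*Protocol article*

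**What the plan says.** The order of events is set in the protocol article, under Treatment allocation and randomization. Dyads go to their "group prior to baseline assessment. Treatment allocation will be centrally randomized using a web-based scheme". What comes before allocation is a background questionnaire and peer matching: "group allocation will be assigned in the order in which participants have completed an initial background and demographics questionnaire". On masking, the same section says "participants cannot be blinded to treatment allocation, the primary investigators and statistician completing data analysis will be blinded".

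Data collection and measures treats the exercise questionnaire as separate from the demographics form: "BCS will complete exercise volume, social support, and HRQOL questionnaires online at four time points: baseline, post 10-week intervention". The 7-day Fitbit wear falls at the same four time points. Under Primary outcome, exercise volume "will be measured using a valid and reliable self-report survey (modified Godin Leisure Time Exercise Questionnaire").

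Baseline MVPA then enters every research question:
- **Model.** The Fig. 1 legend gives "X = Baseline, Y = Post-10 week intervention as primary endpoint".
- **Question 1.** Statistical analysis compares post-intervention means between groups after adjusting for the actor and partner paths, that is, for both women's baseline MVPA.
- **Questions 2 and 3.** Baseline MVPA is the predictor of interest. Partner effects are estimated within each group, and actor effects are compared between groups.

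The Intervention section also requires a self-report of current exercise volume for matching, which must precede allocation. It is not named as the model's baseline.

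**The concern.** A baseline covariate is safe to adjust for because allocation cannot have influenced it. Here the stated order removes that guarantee. The measure is a self-report of the very behaviour that the intervention targets. A woman who already knows that she will, or will not, be coached by an exercise professional could plausibly exercise or report differently in the baseline week. Any between-arm difference created in this way is treated by the model as a pre-existing imbalance and is adjusted out of the treatment effect. The primary comparison is what is at stake, and a baseline collected after allocation is known cannot be collected again.

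**Working it through.** **Inputs.** From Sample size: actor effect 0.33, partner effect 0.28, baseline correlation between peers 0.46, error correlation 0.30, alpha 0.05, power 0.80, and 54 dyads in total. From Treatment allocation: 1:1 by dyad, so 27 dyads per arm. Assumed: d, the shift in reported baseline in one arm, in SD of an individual woman's score. The documents give neither d nor an SD in minutes, so results stay in SD units.

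**The plan's own figure.** This checks that the model is the one the plan used.
- R² = 0.33² + 0.28² + 2(0.33)(0.28)(0.46) = 0.272.
- Variance of each coefficient = (1 - R²)/4 × [(1 + 0.30)/(m(1 + 0.46)) + (1 - 0.30)/(m(1 - 0.46))].
- With m = n - 1, n - 2 degrees of freedom and a two-sided noncentral t test, 80% power needs 32 dyads (actor) and 43 dyads (partner), exactly as stated. A normal approximation gives 29 and 40.

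The point below concerns the order of measurement and does not depend on these numbers of dyads.

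**Bias in question 1.** Averaging the two women in a dyad, the slope of post-intervention MVPA on baseline MVPA is actor + partner = 0.33 + 0.28 = 0.61. The adjusted difference equals the unadjusted difference minus 0.61 times the observed baseline difference. If allocation shifts reported baseline in MatchQEP by d, the bias is -0.61d. The sign reverses if that arm under-reports.

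The false-positive rate was simulated with 27 dyads per arm, no attrition, true effect zero and 4000 runs. The dyad-mean outcome was regressed on arm and dyad-mean baseline at nominal 5%. The third column sets the partner effect to zero, so the slope is 0.33.

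| Size of d (SD) | Size of bias, slope 0.61 (SD) | Size of bias, slope 0.33 (SD) | False-positive rate, slope 0.61 |
|---|---|---|---|
| 0 | 0 | 0 | 5.6% |
| 0.1 | 0.06 | 0.03 | 6.1% to 7.2% |
| 0.2 | 0.12 | 0.07 | 9.7% |
| 0.3 | 0.18 | 0.10 | 15.1% |
| 0.4 | 0.24 | 0.13 | 22.4% to 24.5% |
| 0.5 | 0.31 | 0.17 | 32.4% |

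Where two rates are shown, they are for the two directions of shift. Under the same shifts the group difference not adjusted for baseline stayed within 0.006 SD of zero.

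**Questions 2 and 3.** The actor and partner slopes are estimated within each group. Adding a constant to every baseline score in a group changes the intercept and leaves the slopes alone. They move only if the reaction differs between women in the same arm, for example if the least active react most.

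**The case against.** The strongest objection concerns timing of disclosure. A reader might infer that participants know their group when they complete the baseline questionnaire. The text does not say so. "Although the research coordinator(s), QEPs, and participants cannot be blinded to treatment allocation" describes the trial as a whole, and generating an allocation is not the same as releasing it. The study flow figure is not shown here and cannot settle the matter. This stands: the measure is post-randomisation in any case, but the bias is conditional on disclosure. It does not remove the point, because nothing shown states that allocation is held back.

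The size is also open. The 0.61 comes from a 21-day pilot described as reflecting the Match group. The protocol itself expects weaker stability in MatchQEP and little or no partner effect in controls, so a common slope is a simplification. This too stands, and it is why a range is shown.

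Three stronger readings are tempting and are not supported:
- **That the actor and partner effects are distorted.** A uniform shift within an arm does not do this, and the documents give no evidence of a non-uniform one.
- **That dyads who leave on learning their group would have no baseline information.** They would lack the baseline questionnaire and Fitbit week, but would still have the exercise volume reported for matching.
- **That the full baseline shift passes into the result.** This would be true of a change score. Although the first hypothesis is worded in terms of increases, the stated analysis is an adjusted comparison of post-intervention means.

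That the coordinators are unblinded adds little, since participants complete the questionnaires online themselves. Finally, Descriptive data and covariates calls the demographics form a baseline form. This is loose usage and does not move the exercise questionnaire ahead of allocation.

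**Conclusion.** The point holds in conditional form. The protocol fixes a sequence in which the covariate for the primary comparison, which is also the model's main predictor, is collected after randomisation in a trial without participant blinding, and it states no safeguard. If allocation is known before baseline and shifts reporting by 0.1 to 0.5 SD in one arm, the adjusted difference is biased by 0.06 to 0.31 SD in size, direction unknown. This rests on an assumed d and on the pilot coefficients holding as slopes in both arms. If allocation is in fact concealed until baseline is complete, this source of bias disappears. Damage to questions 2 and 3 is possible but not shown.

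**What to change.** Complete the baseline questionnaires and the 7-day Fitbit wear after matching but before allocation is generated or released to participants and coordinators, and reword the allocation section accordingly. If allocation is already withheld until baseline is complete, one sentence saying so is enough.

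For dyads already randomised who knew their group before baseline, use the exercise volume reported for matching as the covariate for question 1, and add a comparison not adjusted for baseline as a sensitivity analysis. The matching report should not replace baseline in questions 2 and 3. Peers are matched to within 30 minutes per week on it, which would probably raise the within-dyad correlation above the planned 0.46 and make actor and partner effects harder to separate. Nor is it stated to be the modified Godin measure.

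The cost is the wear week plus the time to mail devices across Canada before allocation. No new instrument is needed, and the stated 32 and 43 dyads do not change.

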#### Control condition

BCS in the *Match* (control) group will independently communicate and support each other around exercise for 10 weeks. They will not have any contact with a QEP during this time and will structure their own communication with their matched peer. After the 12 weeks post-intervention follow-up assessment (26 weeks post-baseline), BCS in this group will be offered a single consultation session with a QEP to discuss exercise-related questions.

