### Descriptive data and covariates

Age in years, stage of cancer, time since treatment, time since diagnosis, current medications, and exercise preferences will be self-reported at baseline in an online demographic questionnaire. The Sedentary Behavior Questionnaire [69] will be used to assess the amount of time (in hours) per week spent engaged in sedentary pursuits (e.g., watching television, sitting and reading). The scale has demonstrated reliability and validity in adult populations [69]. Sedentary behavior will be a covariate [70]. Exercise peer match quality (assessed on a 5-point scale from 1: very poor match to 5: very good match), amount of time spent with peer, method of connecting with peer, and perceived similarities with peer (assessed on a 5-point scale from not at all similar to extremely similar) will be collected post-intervention and used as covariates in analyses (see Additional file 3). Therapeutic alliance between participants and the QEP will be assessed by each participant in the *MatchQEP* group at the post intervention (10 week) and post tapering (14 week) time points using the modified Work Alliance Inventory—Short Form Revised (WAI-SR) [71]. The WAI-SR is a twelve-item scale evaluating three domains of therapeutic alliance: (1) agreement between patient and therapist on the goals of treatment, (2) agreement between patient and therapist about the tasks to achieve these goals, and (3) the quality of the bond between the patient and therapist (QEP) [71]. Each item is assessed on a 7-point Likert scale from 0 (never) to 7 (always), with higher scores representing higher satisfaction with the therapist (QEP)-patient relationship [65]. The WAI-SR is a reliable and valid outcome for assessing therapeutic alliance (internal consistency: α = 0.91, test–retest reliability: *r* = 0.93; and construct validity: *r* = 0.74) [71].

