Multiple-group structural equation modeling (SEM) will be used to estimate and test an APIM with two groups (*MatchQEP* vs. *Match*). To address research question 1, the mean post-intervention levels of MVPA (controlling for actor and partner effects) of the two groups will be compared. For research question 2, the average partner (i.e., peer) effects of MVPA from each BCS in the dyad will be estimated within each group [43]. The effects will be tested by comparing constrained and unconstrained models on chi-square goodness-of-fit values. For research question 3, the average actor effects for MVPA among BCS will be estimated for the *MatchQEP* and *Match* groups and will be tested against each other. These analyses will be repeated for device-measured MVPA, social support, and quality of life (secondary outcomes). Measured covariates (e.g., cancer and personal characteristics, partner characteristics and quality of match, therapeutic alliance) will be included in the models as necessary based on their association with the outcomes.

To assess the intervention effects (tertiary outcomes)*,* adherence will be examined based on the number of sessions attended with the QEP in the *MatchQEP* group and on the frequency the peers connected over the duration of the study for both *MatchQEP* and *Match* participants. Cost-effectiveness will be determined by comparing the direct intervention costs between study groups and between the *MatchQEP* group and traditional, in-person QEP services. Additionally, cost-effectiveness of the intervention group, compared to control group, will be calculated based on the intervention costs per participant with respect to changes in the assessed health outcomes. Incremental cost-effectiveness ratios will determine the cost of one unit of change for the investigated outcomes. Mean costs of each category of health resource use (health care facility visits, doctor visits, procedures received, support services used) and loss of work will be calculated for each group and compared for significant differences using *t* tests. All costs will be determined based on current 2021 Ontario Health Care standards in Canadian dollars.

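### The protocol promises a blinded statistician, yet makes therapeutic alliance, collected in MatchQEP only, a candidate covariate for the two-group models, which shows which group is which while covariates are still being chosen

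*Protocol article*

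**What the plan says.** All references are to the protocol article.

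- **Treatment allocation and randomization** accepts that coordinators, QEPs and participants know the allocation, but states without qualification that "the primary investigators and statistician completing data analysis will be blinded".
- **Descriptive data and covariates** limits the alliance questionnaire to one arm, at 10 and 14 weeks: "Therapeutic alliance between participants and the QEP will be assessed by each participant in the *MatchQEP* group".
- **Control condition** says of the Match women: "They will not have any contact with a QEP during this time". A single consultation is offered to them only after the 26-week assessment.
- **Data collection and measures** gives alliance its role: "The QEP alliance (i.e., connection to the QEP support provider) will be assessed as a covariate at post-intervention and post-tapering time points".
- **Statistical analysis** names "partner characteristics and quality of match, therapeutic alliance" among the measured covariates, which "will be included in the models as necessary based on their association with the outcomes". The models in question are a multiple-group structural equation model comparing MatchQEP with Match, repeated for the secondary outcomes.

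The article does not describe a masked first stage, a separate file for variables that exist in one arm only, or a covariate set fixed before such variables are opened.

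**The concern.** Two statements pull against each other. One promises that the analyst does not know the arms. The other asks the analyst to judge whether a variable that exists in one arm only is associated with the outcome, and to build the model accordingly. The analyst cannot do the second without losing the first.

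The timing is what matters. Every analyst learns the arms eventually. Here they become known while the adjustment set is still being selected by looking at outcomes, and the hypotheses are directional. An analyst who knows the arms can, even unintentionally, favour a covariate set that moves the MatchQEP versus Match contrast in the expected direction. The trial would then report a blinded analysis that its own covariate rule had undone.

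A second problem has the same source. Alliance arises after randomisation and has no value in Match, so it has no meaning as an adjustment variable for the comparison of arms in research question 1.

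**Working it through.** The plan gives no figure to reproduce. The check is a comparison of sections with a little arithmetic.

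**Step 1: can alliance exist in Match?** No. The questionnaire is given to MatchQEP participants, and Match women have no QEP contact in the intervention period. Any non-missing alliance score therefore marks a MatchQEP woman and, because dyads are randomised together, her partner too.

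**Step 2: must the analyst hold it while choosing covariates?** Yes, on the text. Selection is by association with the outcomes, so alliance scores must sit beside the outcomes at the screening step. Whether alliance is then kept makes no difference to the unblinding.

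**Step 3: how much is revealed?** Inputs from Sample size: 108 women in 54 dyads and 30% attrition. From Treatment allocation: 1:1 by dyad. Assumption: attrition is equal in the arms and applies to the 10-week questionnaire.

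- Women per arm: 108 / 2 = 54 (27 dyads).
- MatchQEP women with a 10-week score: 0.7 × 54 = 37.8, about 38.
- MatchQEP women without one: 54 − 38 = 16.
- Match women with a score: 0 of 54.

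Two cases follow:

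| File contents | What is revealed |
|---|---|
| Alliance scores, no group code | About 38 women, and any partner of theirs without a score. A dyad with no score in either member looks like a Match dyad. |
| Alliance scores and a masked A/B code | One score shows which letter is MatchQEP, so all 54 dyads are identified. |

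The multiple-group model needs a group code, so the second case is the relevant one. About 38 scores in one coded group and none in the other could not be overlooked.

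**Step 4: could alliance adjust the comparison at all?** Write the post-intervention mean, for own and partner baseline MVPA X and X′ and alliance A, as

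- MatchQEP: a₁ + b₁X + p₁X′ + cA
- Match: a₀ + b₀X + p₀X′

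With A uncentred, a₁ refers to a woman with an alliance score of zero, so a₁ − a₀ is not the treatment contrast. With A centred at its MatchQEP mean, the contrast returns approximately to the one without A, and adjustment has gained nothing. Dropping women with missing A removes all of Match. Setting A to a constant in Match makes it largely a proxy for group. None of these gives an adjusted between-arm effect.

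**The case against.** The strongest reply is that blinding depends on how files are built and released, which a journal article commonly leaves to an analysis or data-management plan. Nothing says that the statistician receives alliance data before the primary comparison, and the covariate sentence is hedged: alliance is an example, to be included as necessary. Part of this stands. Alliance is a candidate covariate, not a certain one, and a staged release could preserve the blinding. But the article puts alliance in the same pool and under the same outcome-driven rule as the other covariates of the two-group models. A staged release that kept it from the analyst would have to depart from that rule, so this is a conflict in the text and not merely an omitted detail.

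Some stronger readings are tempting and are not supported:

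- *QEP attendance also unblinds the main models.* Attendance is a tertiary outcome analysed outside the actor-partner models and is not named as a covariate for them. It need not be in the primary file.
- *Analyst blinding is the only safeguard at the analysis stage.* The primary outcome, its instrument and time point, the model class and the comparison for each research question are all stated. Analyst blinding also does nothing about self-report by unblinded participants.
- *Alliance data alone identify every dyad.* As shown in the working, full decoding also needs the masked group code.
- *The analysis cannot be blinded.* It can, once alliance is removed from the two-arm models.

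**Conclusion.** The concern holds for the statistician's blinding. Followed as written, the covariate rule discloses the arms before the adjustment set is settled, and it admits a variable that cannot serve the between-arm comparison in any case. With a masked group code, disclosure covers all 54 dyads. About 38 alliance scores would be expected at 10 weeks, assuming 30% attrition spread equally over the arms.

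A reader might infer that the primary result will be biased. The document does not show this. The size and direction of any bias depend on choices not yet made and cannot be computed from it. What is established is that the stated protection does not survive the stated method. The conclusion rests on the published text; an analysis plan that fixes the covariates without alliance would resolve it.

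**What to change.** 1. Remove therapeutic alliance from the covariate list of the two-arm models, for research questions 1 to 3 and for the secondary outcomes. Analyse it within MatchQEP only.
2. Fix the two-arm models on baseline covariates, including baseline MVPA, which the actor and partner effects need. These should be called baseline and not pre-randomisation covariates, because dyads are randomised before the baseline assessment.
3. Lock those models under a masked group code before alliance, QEP attendance, QEP contact-hour and event-log data are released to the statistician. Then run the adherence, cost and within-MatchQEP analyses.
4. If this is not done, restate the blinding claim under Treatment allocation and randomization so that it describes what will happen.

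The cost is a small data-handling step and a few sentences, with no change to recruitment, intervention or measures. One consequence should be stated openly: match quality, time with the peer, method of connecting and perceived similarity are collected after the intervention, so they would move to supplementary models. They are planned for both arms, so having them in the file does not by itself reveal the allocation.
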